### Data analysis plan

All data will be reported following the Consolidated Standards of Reporting Trial guidelines.^42^ Baseline clinical and demographic characteristics will be summarised using frequencies and percentages for categorical variables, and means, SD, medians, IQRs and minimum and maximum values for continuous variables, as appropriate. All statistical analyses for the primary and secondary outcomes will follow the intention-to-treat (ITT) principle. The ITT population will include all randomised participants based on their initial assignment to either intervention or control group and include any participants who prematurely withdraw or poorly comply with the protocol.

All primary and secondary analyses will use Generalised Estimating Equations with pharmacy as the unit of clustering, using the model appropriate for the distribution of the outcome. The analysis of the primary outcome (reported as a binary variable 0=not diagnosed with CKD, 1=diagnosed with CKD) will use a logistic regression within a model to test the effectiveness of the intervention. Analysis will first be unadjusted (including as fixed factors group membership and the stratification variable, region), followed by analysis adjusted for relevant baseline covariates (age, gender, blood pressure measures, BMI, socioeconomic status and location of pharmacies), as well as the fixed factors from the unadjusted analysis. Binary secondary outcomes such as percentage of participants with CKD risk factors, those having a GP review, and those with potentially inappropriate medications will be analysed using a similar approach as that for the primary outcome.

Additional outcomes including numbers of recommendations made by pharmacists, numbers of medication-related hospitalisations or acceptance rates by GPs will be analysed using negative binomial regression (or Poisson regression, depending on distribution of the outcome) or logistic regression and will include unadjusted and adjusted analyses as per the primary outcome.

For humanistic outcomes such as participant’s health-related quality of life, as well as outcomes on GP satisfaction and participant knowledge/satisfaction, we will use linear regression. All analyses will be presented using unadjusted and adjusted models as per the primary outcome. For the proportion of participants screened in the trial (process indicator), we will use the Mantel-Haenszel extension of a χ^2^ Test of Independence.

The proportion of missing data will be determined and assessed for any patterns related to the missingness. Unless otherwise stated, multiple imputation (MI) will be used to impute missing values. Missing dichotomous data and categorical data with >2 categories will be assessed using the appropriate MI regression techniques, and missing continuous data will be imputed using chained equations. Sensitivity analyses to explore the effect of imputation will be conducted (eg, complete case; assuming worst case for the missing outcome observations). All tests will be two-sided, with statistical significance set at 0.05 and we will use IBM SPSS Statistics for all analyses unless otherwise specified. There will be no adjustment of the alpha level to account for multiple comparisons because the primary and secondary outcomes are specified, unless otherwise stated to be post hoc.

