**Methods and analysis:**

This study is a multicentre, pragmatic, two-level cluster randomised controlled trial which will be conducted across different regions in Australia. Clusters of community pharmacies from geographical groups of co-located postcodes will be randomised. The project will be conducted in 122 community pharmacies distributed across metropolitan and rural areas. The trial consists of two arms: (1) Control Group: a risk assessment using the QKidney CKD risk assessment tool, and (2) Intervention Group: a risk assessment using the QKidney CKD plus Point-of-Care Testing for kidney function markers (serum creatinine and estimated glomerular filtration rate), followed by a QUM service. The primary outcomes of the study are the proportion of patients newly diagnosed with CKD at the end of the study period (12 months); and rates of changes in the number of medications considered problematic in kidney disease (number of medications prescribed at inappropriate doses based on kidney function and/or number of nephrotoxic medications) over the same period. Secondary outcomes include proportion of people on potentially inappropriate medications, types of recommendations provided by the pharmacist (and acceptance rate by general practitioners), proportion of people who were screened, referred, and took up the referral to visit their general practitioners, and economic and other patient-centred outcomes.

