## Methods

### Study setting and design overview

This study protocol is a multicentre, pragmatic, two-level cluster randomised controlled trial. The reporting of this protocol has been guided by the checklist outlined in the Standard Protocol Items: Recommendations for Interventional Trials (SPIRIT statement, online supplemental appendix 1).^31^

10.1136/bmjopen-2023-079110.supp1Supplementary data

Community pharmacies (clusters) are the unit of randomisation and screening participants are the unit of analysis. The project will be conducted in community pharmacies across three Australian states of New South Wales (NSW), Victoria (VIC), and Queensland (QLD) and later expanded to the Australian Capital Territory.

Community pharmacies will be selected from geographical groups of co-located postcodes to form clusters within the top 50 kidney disease hotspot areas identified by Kidney Health Australia.^14^ Co-located pharmacies within a cluster represent a local community that will all receive the same service model to reduce contamination bias. Pairs of clusters matched by characteristics such as location and socioeconomic status^32^ will be randomly allocated to the intervention or control groups. Objective geographical access is described using the Modified Monash Model (MMM). Consistent with the Australian Government Department of Health and Aged Care’s definition used in the Rural Health Multidisciplinary Training Program,^33 34^ the MMM for this study was broadly stratified into Metropolitan (MM1) and Rural (MM2–7) categories. Given there were no postcodes classified as ‘MM6 – Remote Communities’ or ‘MM7 – Very Remote Communities’ identified within the top 50 kidney disease hotspots, the Rural categorisation was constrained to MM2–5. The number of community pharmacies to be targeted is determined based on the respective population sizes of the states, with proportional pharmacy distributions across Metropolitan and Rural settings. Therefore, based on the population of the states and the percentage contribution of each state, a total of 122 community pharmacies will be recruited from the three states with 1:1 control:intervention allocation, representing 50 pharmacies from NSW (38 Metropolitan vs 12 Rural), 40 from VIC (30 vs 10) and 32 from QLD (20 vs 12). Given the proximity of some of the NSW pharmacies, we have expanded our recruitment to include pharmacies in the Australian Capital Territory.

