#### Sample size

Sample size selection and estimation was performed based on the CKD diagnosis. Using the GRT sample size calculator,^35^ it is estimated that the intervention will increase diagnosis from the current CKD prevalence of 10% to between 15% and 20%, an increase of 5%–10%. Sample size is estimated based on a 5% increase in diagnosis of CKD. With 80% power, alpha of 0.05 and intraclass correlation coefficient (ICC)=0.05, at least 57 clusters are required per arm. Based on our sampling model, cluster size has been increased to 61 per arm to account for attrition. With an average number of 30 participants per cluster, the total sample size to be targeted is 3660. Based on previous study^11^ that showed a reduction of inappropriate medications in CKD from 32.3% to 17.5% (an approximate reduction of 15%), with 90% power, alpha=0.05 and ICC of 0.05 and a cluster size of 30 per cluster, 19 clusters in each arm are required (38 clusters in all) with a sample size of 1140 for the other primary outcome, that is, change in inappropriate medication use. The sample size required for the diagnosis outcome is, therefore, sufficient to cover the sample size required for the medication changes outcome.

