#### Costs analysis

The cost per new CKD case diagnosis for each group will be estimated and compared. We will assess whether the average cost of the new CKD case diagnosis in the intervention group is lower or higher than the average cost of the new CKD case diagnosis in the control group. We hypothesise that there is likely to be a difference in average costs per new CKD case diagnosis across the sites in the same cluster and across the clusters from the metropolitan and rural settings. This is due to the differences in sample size, local unit prices of equipment, staff costs and different established local practices.

Differences in overall mean costs between the two groups will be analysed using Generalised Linear Mixed Model. The distribution of residuals from the regression model will be examined and a decision will be made as to whether the costs should be logarithm transformed. Any extreme costs will be carefully examined to decide if they should be considered as extreme outliers and should be trimmed (removed) from the analysis. It is anticipated there will be some missing data. Missing costs data will be examined to ascertain whether it is missing completely at random, missing at random or missing not at random. Simple and multiple imputation methods will be considered based on the pattern of missingness.^45^

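### The protocol contradicts itself on the randomised unit: most of the design text allocates geographical groups of pharmacies, but the sample size and the GEE treat each pharmacy as an independent cluster

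*Protocol article*

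**What the plan says.** Three places in the protocol article describe a cluster that holds several pharmacies.

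- Abstract, Methods and analysis: "Clusters of community pharmacies from geographical groups of co-located postcodes will be randomised".
- Study setting and design overview: "Community pharmacies will be selected from geographical groups of co-located postcodes to form clusters", and then "Co-located pharmacies within a cluster represent a local community that will all receive the same service model to reduce contamination bias". The next sentence allocates "Pairs of clusters matched by characteristics such as location and socioeconomic status" at random to the two arms.
- Costs analysis: average costs are expected to differ "across the sites in the same cluster and across the clusters from the metropolitan and rural settings".

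Three places treat the single pharmacy as the cluster.

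- Study setting and design overview, before the sentences above: "Community pharmacies (clusters) are the unit of randomisation and screening participants are the unit of analysis".
- Sample size: "at least 57 clusters are required per arm", raised to 61 for attrition, with 30 participants in each and 3660 in total.
- Data analysis plan: "All primary and secondary analyses will use Generalised Estimating Equations with pharmacy as the unit of clustering". The unadjusted model has arm and region as fixed factors. The adjusted model adds patient covariates, socioeconomic status and pharmacy location. Neither contains the matched pair or the geographical group.

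The article calls the design two-level but does not say which levels are meant. It does not give the number of geographical groups.

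**The concern.** A cluster-robust GEE variance is valid when the units it clusters on are independent of one another. If the arm is assigned to a whole group of neighbouring pharmacies, the pharmacies in that group share the arm by design. Any remaining similarity between them then adds to the variance of the arm comparison, and a variance clustered on pharmacy does not see it.

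Some similarity is plausible. The design section treats co-located pharmacies as one local community and gives them one arm to limit contamination. The primary outcomes come from GP records, and nearby pharmacies may well refer to the same practices. The documents do not quantify this.

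At stake are the standard errors, confidence intervals and p values of both primary outcomes, and the stated power for CKD diagnosis. This is not a detail left open for a later analysis plan, because the article fixes the clustering level for every primary and secondary analysis.

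**Working it through.** **Inputs from the protocol.** 10% v 15% diagnosed, 80% power, alpha 0.05, ICC 0.05, 57 clusters per arm raised to 61, 30 per cluster, total 3660 (Sample size). Tests are two-sided (Data analysis plan). 122 pharmacies are allocated 1:1 (Study setting and design overview).

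**Inputs not given, so assumed.** The number of geographical groups G, and the correlation ρ between participants of different pharmacies in the same group.

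**1. Which cluster does the sample size use?** 61 × 2 × 30 = 3660 = 122 pharmacies × 30. Its cluster is one pharmacy.

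**2. Reproducing the stated figure.**
- Individually randomised n per arm: [1.960·√(2 × 0.125 × 0.875) + 0.842·√(0.10 × 0.90 + 0.15 × 0.85)]² / 0.05² = 685.6, so 686.
- Design effect: 1 + 29 × 0.05 = 2.45.
- Clusters per arm: 686 × 2.45 / 30 = 56.02, so 57, as stated.
- Power at 61 per arm is 83%.

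The figure is right if pharmacies are independent. No correlation between pharmacies enters it.

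**3. Adding the group level.** With k = 122/G pharmacies per group:
- Design effect D = 2.45 + (k − 1) × 30 × ρ.
- Type I error of the pharmacy-level test at nominal 5%: 2·[1 − Φ(1.96·√(2.45/D))].
- Power of a test that respects the groups: SE = √[(0.09 + 0.1275) × D / 1830], where 1830 = 61 × 30, and a noncentral t with G − 2 degrees of freedom.

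Example, G = 50 and ρ = 0.01: k = 2.44; D = 2.45 + 1.44 × 30 × 0.01 = 2.88; √(2.45/2.88) = 0.922; type I error 7.1%; SE = 0.0185; power 75.4%.

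| Groups | k | ρ | D | Type I error | Power |
|---|---|---|---|---|---|
| any (independent pharmacies) | – | 0 | 2.45 | 5.0% | 83% |
| 60 | 2.03 | 0.005 | 2.60 | 5.7% | 79.8% |
| 60 | 2.03 | 0.01 | 2.76 | 6.5% | 77.5% |
| 50 | 2.44 | 0.01 | 2.88 | 7.1% | 75.4% |
| 50 | 2.44 | 0.025 | 3.53 | 10.2% | 66.7% |
| 30 | 4.07 | 0.025 | 4.75 | 15.9% | 52.9% |

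The table assumes groups of equal size, all 61 pharmacies per arm retained, and no use of the matching. The last row combines the fewest groups with the highest correlation, and nothing in the documents points to it in particular.

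**4. The medication outcome.** The protocol asks for 19 clusters per arm at 90% power with the same ICC and cluster size. At the largest design effect above, 19 × 4.75 / 2.45 = 36.8, so 37. Using t with 28 degrees of freedom multiplies this by (2.048 + 1.313)² / (1.960 + 1.282)² = 1.075, giving about 40. Both are below 61.

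**The case against.** **The pharmacy may have been randomised.** One sentence says so, and it agrees with the sample size and the GEE. This stands as far as it goes, and a reader who infers that group randomisation is settled goes beyond the text. But the same section says that co-located pharmacies share an arm and that pairs of clusters are allocated, which independent allocation of pharmacies would not produce. On either reading some part of the article is wrong.

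**The consequence is conditional.** A reader might infer that the standard errors are certainly too small and that 80% power is certainly not reached. The documents do not support that. It requires more than one pharmacy per group, which the design text indicates without numbers, and a positive residual correlation, which no section reports. With two pharmacies per group and ρ = 0.005, power stays at about 80% with all 61 per arm, although the margin from 57 to 61 was set aside for attrition.

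**Matching works the other way.** Area variance shared by the two groups of a pair cancels from the arm comparison, while an unadjusted pharmacy-level variance still counts it. If the pair accounts for a fraction φ of the area variance, the area contribution is proportional to k(1 − φ) in truth and to 1 in the pharmacy-level variance. That variance is too small only if φ < (k − 1)/k: 51% at 60 groups, 59% at 50 and 75% at 30. The covariates of the adjusted model may also remove some correlation. This stands. It makes understatement likely rather than established, and the table is illustrative for that reason.

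**Both primary outcomes underpowered?** A reader might infer this too. Step 4 shows that the stated power for the medication outcome survives even the worst case considered.

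**Conclusion.** The contradiction is certain and can be read from the text. Most of the design description randomises geographical groups in matched pairs. One design sentence, the sample size and the GEE use the pharmacy.

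The statistical consequence holds under two conditions: groups were randomised, and pharmacies within a group are positively correlated beyond what matching and covariates remove. The planned intervals and p values for both primary outcomes are then too optimistic, and the power for CKD diagnosis is overstated. The direction is clear under those conditions, but the size cannot be fixed from the documents. The illustrated range runs from no loss at zero correlation to a type I error of 16% and power of about 53% with 30 groups and ρ = 0.025, all for an unmatched comparison.

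**What to change.** 1. **Study setting and design overview:** name one unit of randomisation, and bring the abstract, Sample size, Data analysis plan and Costs analysis into line with it. The allocation is reported in the past tense, so the sponsor can establish which unit was used.
2. **Data analysis plan, if the unit is the geographical group:** cluster the GEE on the group, or fit a mixed model with pharmacy nested in group. Reflect the matched pairs in the model, and use a small-sample correction based on the number of groups or pairs.
3. **Sample size, if the unit is the geographical group:** state the number of randomised groups, and restate the power for CKD diagnosis with both the within-pharmacy and the between-pharmacy correlation, over a range for the latter.
4. **If pharmacies were allocated independently:** correct the sentences that say otherwise, including the claim that a shared arm limits contamination. The planned clustering level can then stay.

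The cost is wording, a change of analysis level and a recomputed power statement. Under group randomisation, intervals are likely to become somewhat wider and the stated power lower. The correction needs no extra patients.

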Following recruitment, screening participants in the ***control*** group, if they are known patients with CKD (stages 1–4; based on self-report), will be provided with lifestyle advice and counselling on medications to avoid in kidney disease along with a Kidney Health Australia factsheet on ‘Looking after yourself with kidney disease’. All other control group patients will have their risk of developing CKD computed using the QKidney risk calculator,^38^ or based on blood pressure levels, if they have at least one of the known CKD risk factors. Participants will be advised of an appropriate action based on their calculated risk. All participants will be provided with lifestyle advice using a range of educational fact sheets, sourced from Kidney Health Australia resources, targeting their risk factors for CKD.

Following recruitment, participants in the ***intervention*** group will be divided into two groups.

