Screened participants in the intervention group are expected to attend a pharmacy session lasting between 20 and 45 mins with the trained pharmacist to assess and collect basic demographic and clinical/medical information (eg, height, weight, blood pressure, medications dispensed), and to apply the QKidney Risk assessment and POCT protocol and operating procedures. The time it takes for the overall procedure depends on the individual participant’s circumstances, such as the presence of pre-existing CKD or level of risk of developing it, type and number of medications involved as well as the need for screening referral to a GP. Similarly, participants in the control group will be expected to attend a pharmacy session at baseline lasting between 20 and 30 mins for the relevant risk assessment using the QKidney Risk tool and to provide relevant education and resources pertinent to their level of risk and risk factors for CKD.

Participants in the intervention group will be followed up by pharmacists/research project officers via phone or SMS (short messaging service) at 6 weeks to determine the status of the recommended follow-up with the GP and to re-advise GP review if participants have not yet made an appointment with their GP. All participants will be followed-up by pharmacists/research officers at 6 months and 12 months to determine the number of medications changed and new cases of CKD diagnosed (in participants with no prior history).

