### Data collection, monitoring, management and reporting

Data collection is purpose designed and will be facilitated by a highly secured and password protected online software application. Study protocols, templates for assessing CKD risk, links to the QKidney risk calculator, template for GP referral, QKidney health advice, template for QUM service will be included in the software along with specific guides to support access and familiarisation. Intervention group pharmacies will also be able to record the POCT results in the software. This will maximise trial efficiency and reduce the burden on pharmacists.

Adherence to the study protocol will be regularly monitored for accuracy and completeness by the project manager and research officers using the online study website and site visits. In addition, project officers will use a range of communication strategies to ensure that the community pharmacists are kept informed of the latest developments of the study, and to provide ongoing support to the pharmacists and these include regular phone calls and bulk emailing options to allow an early action where pharmacies require additional support with the study.

Data collection including pre-screening, screening and post-screening activities and the respective time points are outlined in table 1. The study is set to take place over 2 years (March 2023 to May 2025), and will include enrolling pharmacists and patients, 6-month and 12-month follow-ups and report writing.

**Table 1 T1:** Study procedures and time points

Procedure	Baseline	6 weeks	3 months	6 months	12 months
Pre-screening/screening activities					
Site randomisation	X				
Information sheet	X				
Pharmacist/participant consent	X				
Initial screening	X				
Pharmacy survey (current services)	X				
Inclusion/exclusion criteria - review	X				
Demography and medical history	X				
Outcome assessment					
Proportion of people with CKD				X	X
Changes in # of PIMs				X	X
% of participants with CKD risk factors	X			X	X
QKidney risk profiles	X				
% Participants referred to GP	X				
% Participants taking up referral with GP				X	X
Phone/SMS reminder (PO/RA)		X			
Other outcomes (health-related quality of life, well-being)	X				X
Study evaluations					
Economic evaluation (health resource use and costs)					X
Pharmacist midtrial Interview			X		X
Pharmacist end of trial interview					X
GP satisfaction					X
Participant knowledge/satisfaction survey					X
Study compliance audit	X		X	X	X

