### Outcomes

#### Primary outcome measures

Proportion of patients newly diagnosed with CKD at the end of the study period.Changes in the number of medications considered problematic in kidney disease (number of medications prescribed at inappropriately high dose, number of contraindicated medications or detrimental drug interactions).

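### The first primary outcome is new CKD diagnosis, but the analysis set, event coding and assumed control rate are not tied to participants without CKD at entry, so the stated power is not shown for it

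*Protocol article*

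**What the plan says.** All places are in the protocol article.

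- **Definition.** Primary outcome measures gives "Proportion of patients newly diagnosed with CKD at the end of the study period". The abstract says the same and sets the period at 12 months.
- **Follow-up.** The Clinical protocol and recruitment procedure section says that the 6- and 12-month contacts look for "new cases of CKD diagnosed (in participants with no prior history").
- **Enrolment.** Of people with kidney disease, eligibility bars only those with kidney failure or on kidney replacement therapy. Control participants follow a separate pathway "if they are known patients with CKD" (stages 1–4, by self-report). The intervention arm has a matching pathway.
- **Analysis set.** Data analysis plan: "The ITT population will include all randomised participants based on their initial assignment to either intervention or control group".
- **Coding.** The same section states: "The analysis of the primary outcome (reported as a binary variable 0=not diagnosed with CKD, 1=diagnosed with CKD) will use a logistic regression". Table 1 labels the outcome "Proportion of people with CKD".
- **Source.** Primary outcomes come from GP data (Secondary outcome measures section), while prior CKD is self-reported.
- **Sample size.** "it is estimated that the intervention will increase diagnosis from the current CKD prevalence of 10% to between 15% and 20" per cent. The calculation uses the 5-point rise, 80% power, alpha 0.05, ICC 0.05 and 30 participants per cluster. It gives 57 clusters per arm, raised to 61 for attrition, and 3660 participants.

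**The concern.** A person with known CKD cannot be newly diagnosed. The outcome definition and the follow-up text imply that such people are outside the denominator. The analysis text puts every randomised participant in and drops the word that marks the event as new. Three analyses are therefore compatible with the article: known cases excluded, kept as non-events, or counted as events. They estimate different things and differ in power. If the choice is still open when the data are in, it can be made with the results in view.

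The sample size has the same gap. A prevalence is the share of people who have the disease. The control rate needed here is the share of people without a CKD diagnosis at entry who receive one within 12 months. The calculation also treats all 30 participants per pharmacy as able to have the event.

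Finally, prior history and outcome come from different sources. The text leaves open how to treat a diagnosis that was already on the GP record but that the participant did not report.

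**Working it through.** **Step 1. The plan's own figure.** For 10% v 15%, two-sided alpha 0.05 and 80% power, the pooled two-proportion formula gives 686 per arm. The design effect is 1 + (30 − 1) × 0.05 = 2.45. Clusters per arm = 686 × 2.45 / 30 = 56.02, rounded up to 57. The unpooled form with t quantiles on 2(g − 1) degrees of freedom also gives 57. Total: 61 × 2 × 30 = 3660. The arithmetic is right.

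**Step 2. Power formula.** With g clusters per arm, m evaluable per cluster and rates p1 and p2:

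SE = √{[p1(1 − p1) + p2(1 − p2)] × [1 + (m − 1) × 0.05] / (g × m)}

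Power = P(T ≤ |p2 − p1|/SE − t0.975), with T on 2(g − 1) degrees of freedom.

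At m = 30 this gives 80.2% with g = 57 and 82.8% with g = 61.

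**Step 3. Three treatments of known CKD.** The document gives no share k with known CKD, so k = 5%, 10% and 20% are assumptions. True new-diagnosis rates are kept at 10% v 15% and g = 61.

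- Excluded: rates 0.10 v 0.15, m = 30(1 − k).
- Non-events: rates 0.10(1 − k) v 0.15(1 − k), m = 30.
- Events: rates k + 0.10(1 − k) v k + 0.15(1 − k), m = 30.

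| Known CKD | Excluded (m; power; OR) | Non-events (rates; power; OR) | Events (rates; power; OR) |
|---|---|---|---|
| 5% | 28.5; 82%; 1.59 | 9.5 v 14.25%; 81%; 1.58 | 14.5 v 19.25%; 68%; 1.41 |
| 10% | 27; 81%; 1.59 | 9 v 13.5%; 78%; 1.58 | 19 v 23.5%; 56%; 1.31 |
| 20% | 24; 79%; 1.59 | 8 v 12%; 73%; 1.57 | 28 v 32%; 39%; 1.21 |

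Example, k = 10%, coded as events: SE = √{[0.19 × 0.81 + 0.235 × 0.765] × 2.45 / 1830} = 0.0211. Then 0.045/0.0211 = 2.13, and 2.13 − 1.98 = 0.15, which gives 56%.

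**Step 4. A control rate that is not a prevalence.** The document gives no 12-month new-diagnosis rate, so 2% and 5% are assumptions (g = 61).

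| Control rate | +5 points, m = 30 | +5 points, m = 27 | 1.5-fold ratio, m = 27 |
|---|---|---|---|
| 2% | 99.6% (2 v 7%) | 99.5% | 22% (2 v 3%) |
| 5% | 95.5% (5 v 10%) | 94.7% | 49% (5 v 7.5%) |

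The sign of the error depends on whether the absolute or the relative effect carries over to a lower control rate.

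**The case against.** The article's intent is fairly clear. The abstract, the hypotheses and the outcome list all speak of new or previously unknown cases, and follow-up is limited to people with no prior history. The 0/1 coding may be shorthand for that outcome. Table 1 marks its row at 6 and 12 months and not at baseline, which fits new cases. Under the follow-up restriction the power is 79–82%, close to the planned 80%. The article is also condensed, and rules for dating GP records usually sit in a fuller document.

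Most of this stands. A reader might infer that known cases will be counted as events, so that the outcome fails to measure new diagnoses. The document does not say so, and the 68/56/39% column describes one literal reading. A reader might also infer that the power statement is void or the trial underpowered. That does not follow either: the calculation is correct for its inputs, and the sample size section plans on a 5-point rise, for which a lower control rate raises power. Nor does any text say that older GP-recorded diagnoses will count as new.

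What the objection does not remove is the conflict. The article does not leave the analysis set and coding to another document. It states both, and neither matches its own outcome definition. The prevalence is likewise stated as the control rate.

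**Conclusion.** The point holds as an unresolved conflict. The event, the denominator and the control rate of the first primary outcome are not consistent across the outcome definition, the follow-up text, the Data analysis plan and the sample size section.

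The size depends on the reading. With 10% v 15%, 61 clusters per arm, ICC 0.05 and an assumed 5–20% with known CKD, exclusion costs little. Keeping known cases as non-events lowers power to as little as 73% and leaves the odds ratio almost unchanged. Coding them as events lowers power to as little as 39% and the odds ratio to 1.21. The 80% power is arithmetically sound but not demonstrated for new diagnosis, and the direction of the error from using a prevalence is unknown. All these figures use the full 61 clusters, so they assume that none of the attrition allowance is used up.

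**What to change.** 1. **Primary outcome measures and Data analysis plan:** define the event as a CKD diagnosis first recorded by the GP after enrolment and by 12 months.
2. **Data analysis plan:** analyse this outcome by allocated arm in participants with no CKD before enrolment, meaning no self-reported CKD and no earlier diagnosis in the GP record. Apply the same record check in both arms. Because this restriction uses pre-enrolment status, it is compatible with analysis by allocation.
3. **Sample size:** replace the 10% prevalence with an assumed 12-month new-diagnosis rate in that set. Restate the power or detectable difference at the reduced evaluable number per pharmacy, without enrolling more.

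The cost is a few sentences and one recalculation before the data are analysed. Consent to obtain GP records is already part of enrolment. The drawbacks are a somewhat smaller evaluable number (for example 27 instead of 30 per pharmacy if 10% have known CKD) and a power figure that may turn out less favourable.
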